# CERAMENT treatment of fracture defects (CERTiFy): protocol for a prospective, multicenter, randomized study investigating the use of CERAMENT™ BONE VOID FILLER in tibial plateau fractures

**DOI:** 10.1186/1745-6215-15-75

**Published:** 2014-03-08

**Keywords:** bone graft, bone substitute, bone void, fracture, quality of life, pain

## Abstract

**Background:**

Bone graft substitutes are widely used for reconstruction of posttraumatic bone defects. However, their clinical significance in comparison to autologous bone grafting, the gold-standard in reconstruction of larger bone defects, still remains under debate. This prospective, randomized, controlled clinical study investigates the differences in pain, quality of life, and cost of care in the treatment of tibia plateau fractures-associated bone defects using either autologous bone grafting or bioresorbable hydroxyapatite/calcium sulphate cement (CERAMENT™|BONE VOID FILLER (CBVF)).

**Methods/Design:**

CERTiFy (CERament™ Treatment of Fracture defects) is a prospective, multicenter, controlled, randomized trial. We plan to enroll 136 patients with fresh traumatic depression fractures of the proximal tibia (types AO 41-B2 and AO 41-B3) in 13 participating centers in Germany. Patients will be randomized to receive either autologous iliac crest bone graft or CBVF after reduction and osteosynthesis of the fracture to reconstruct the subchondral bone defect and prevent the subsidence of the articular surface. The primary outcome is the SF-12 Physical Component Summary at week 26. The co-primary endpoint is the pain level 26 weeks after surgery measured by a visual analog scale. The SF-12 Mental Component Summary after 26 weeks and costs of care will serve as key secondary endpoints. The study is designed to show non-inferiority of the CBVF treatment to the autologous iliac crest bone graft with respect to the physical component of quality of life. The pain level at 26 weeks after surgery is expected to be lower in the CERAMENT bone void filler treatment group.

**Discussion:**

CERTiFy is the first randomized multicenter clinical trial designed to compare quality of life, pain, and cost of care in the use of the CBVF and the autologous iliac crest bone graft in the treatment of tibia plateau fractures. The results are expected to influence future treatment recommendations.

**Trial registration number:**

ClinicalTrials.gov: NCT01828905

## Background

### Background and rationale

Tibial plateau fractures (TPF) are caused by both low-energy or high-energy excessive varus or valgus forces combined with axial stress on the knee [1]. High-energy fractures are commonly the result of traffic accidents, falls, or sports-related injuries. Low-energy fractures are mainly seen in older individuals due to reduced bone mineral density and are typically associated with a depression of the articular surface. In all cases, depressed articular components require meticulous anatomical reduction and stable osteosynthesis to allow early rehabilitation. The depression of the articular surface may be associated with a metaphyseal defect, which often requires additional reconstruction procedures with autologous bone grafts or bone graft substitutes to improve healing and prevent subsidence of the articular surface [2]. Due to its favorable biological and biomechanical features [3-5], autologous iliac bone grafting (AIBG) has been considered a gold standard especially to reconstruct bone voids of large sizes and fracture non-unions even in metaphyseal and diaphyseal areas. However, some well-recognized complications associated with graft harvesting including pain at the donor site, nerve injury, hematoma, infection and pelvic fracture at the donor site [6-8] may significantly influence the quality of life (QoL) of those patients [9]. In addition, both prolonged operation time and hospital stay after bone graft harvesting may unnecessarily complicate the surgical treatment [9,10].

To address such shortcomings and to develop a non-invasive alternative to AIBG, the quality of synthetic bone graft substitutes has been increasingly improved in the last two decades [11]. In a non-controlled cohort study with a mean follow-up of 22.2 months bone union was achieved in all patients and remodeling of the bone substitute in 89% in depressed tibia plateau fractures [12]. In a prospective, randomized study on 119 patients with tibia plateau fractures treated with a bioresorbable calcium phosphate cement or autologous iliac bone graft the authors showed comparable union rates and times to union in the two groups. Interestingly, a significantly higher rate of articular subsidence was observed in the bone graft group [13].

Other studies on this topic focused on clinical and functional outcomes [14]. Bioactive glass has been compared to autologous bone in a randomized clinical study for the treatment of tibia plateau fractures. This study with 25 patients found the same clinical outcome in the two groups [15]. Clinical and functional outcome parameters have been investigated to compare autologous bone grafts and bone graft substitutes in several studies. However, the endpoints used in these studies were strongly related to the quality of the surgery rather than to the quality of the bone graft material itself. None of the published studies investigated parameters such as pain, quality of life or cost of care, which may really reflect the consequences of the bone harvesting. On the other hand these parameters are also suitable to assess the effects of the bone substitute material quality, which is critical for the defect healing and prevention of the secondary subsidence of the joint surface. Therefore, investigation of these outcome parameters in a sufficiently powered, prospective, randomized, controlled clinical trial is highly necessary.

CERAMENT™ BONE VOID FILLER (CBVF) is one of the widely used bone substitute materials, which was reported to promote cancellous bone healing and reproducible remodeling in bone defects [16]. It consists of 60% calcium sulfate (CS) and 40% hydroxyapatite (HA) and has been previously investigated in an open wedge radius osteotomy study showing convincing results. The aim of this study is to compare the impact of CBVF and autologous bone graft on QoL, pain, and costs of care in a standardized tibial plateau fracture (AO-Types 41-B2 and AO 41-B3 (Figure 1)) that are associated with a significant bone defect.

**Figure 1 F1:**
[figure not shown]
**AO classification of tibia plateau fractures (B2 and B3).** (‘Copyright by AO Foundation, Davos, Switzerland - Müller AO Classification of Fractures’).

### Primary hypothesis

We assume that six months after surgical treatment no relevant mean differences will be present for the SF-12-PCS (Short Form 12 Physical Component Summary Score) and that pain level (determined by Visual Analog Score, VAS) will be lower in patients treated with CBVF compared to autologous cancellous bone grafts in tibia plateau fractures types AO 41-B2 and AO 41-B3.

## Methods/Design

The CERTiFy (CERament treatment of Tibial Fracture defects) trial is a prospective, open-label, multicenter, controlled, randomized clinical trial. The study will comprise 136 patients with acute traumatic depression fractures of the proximal tibia (limited to AO type 41-B2 & B3) from 13 different trauma centers in Germany. Patients are randomized to receive either an autologous cancellous bone graft taken from the iliac crest or CBVF.

### Eligibility criteria

Patients between the age of 18 and 65 years with a solitary, acute, traumatic, closed depression fracture of the proximal tibia (limited to AO types 41 B2 & B3, Schatzker types II and III) (Figures 2, 3, and 4) requiring reconstruction of the subchondral bone void are enrolled into the trial. The ability to understand the procedure of participating in the study and to comply with the follow-up program is a prerequisite. Only patients with a maximum interval of one week between injury and intervention will be included.

**Figure 2 F2:**
[figure not shown]
Anteroposterior (a-p) X-ray of the knee showing an AO 41 B3.1 fracture type.

**Figure 3 F3:**
[figure not shown]
Lateral X-ray of the knee showing an AO 41 B3.1 fracture type.

**Figure 4 F4:**
[figure not shown]
Coronal reconstructions of a computed tomography (CT) scan of the knee showing an AO 41 B3.1 fracture type.

Patients will be excluded from the study if the responsible surgeons request treatment in which the principle of therapeutic uncertainty is violated. Clinical exclusion criteria involve patients with more than one injury, polytrauma patients, compartment syndrome, previous iliac crest bone graft harvesting, local infection at the site of implantation, chronic pain disease, malignancy, rheumatoid arthritis, chronic cortisone therapy, unavailable X-ray diagnostics, doubtful fracture classification, and clinically significant unstable medical or surgical conditions that may preclude safe and complete study participation.

Device-related exclusion factors are pre-existing calcium metabolism disorders (for example, hypercalcemia), hyperthyroidism, or autonomous thyroid adenoma, a history of serious reaction to iodine-based radio contrast agents, pregnancy or breastfeeding (a pregnancy test will be performed at screening visit), irreversible coagulopathy or bleeding disorders, history of physical or psychological condition that contraindicates the use of an investigational device or render the patient at high risk from treatment complications, as well as history of hypersensitivity to the device or any of its ingredients. Participation in other clinical trials during the present clinical trial or within the last month will be also considered an exclusion criterion.

### Randomization

After giving consent to participate in the study, patients will be randomized by a web-based randomization tool provided by IZKS Mainz allowing investigators to randomize patients via a secure web interface. Randomization will be stratified by age group (18 to 39 years; 40 to 65 years) and gender. Block randomization with variable block sizes will be applied.

### Interventions

All fractures will be immobilized with a plaster cast until surgical treatment. Centers may follow their preferred standard operating procedures and locally established protocols for pain management. These modalities will be precisely documented.

### Operative treatment

After randomization, all patients will be operated as soon as possible, depending on local soft tissue conditions, hematoma, and swelling. Open reduction and internal fixation will be performed via an anterolateral approach using screws and buttress plate for stabilization after reduction of the depressed articular surface according to the AO principles of fracture care. The protocol does not specify the use of specific hardware. The bone defect, which is created after reduction of the depressed articular fragments, will be reconstructed either with an autologous cancellous bone graft from the iliac crest or with the CBVF (Figures 5 and 6). All surgeons performing the operation have proven expertise with the procedure and are familiar with the implants and devices used in this study.

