#### V1 - screening visit and randomization

The trial aims and procedures will be explained to the patient by responsible local investigators using a study information booklet. After informed consent is given, the screening visit (V1) will be performed within 7 days prior to day of surgery (day 0). After radiological assessment of the fracture type, baseline demographics, comorbidity, medication, and pregnancy test (if applicable) will be evaluated and verification of inclusion and exclusion criteria performed. The trial participant will be electronically randomized to one of the two treatment arms using a web-based tool. All data will be documented using an electronic case report form (eCRF). Assessment of the VAS and SF-12v2 scores will be performed at the end of the V1.

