### Analysis populations

The intention to treat (ITT) population comprises all randomized patients, even if the planned surgery/surgeries did not take place. The modified intention to treat (mITT) population includes all randomized patients for which the primary endpoint could be assessed (that is, SF-12 PCS assessment is available both preoperatively and 26 weeks after surgery). Patients are eligible for the per protocol (PP) population, if they fulfill the following criteria: eligible for the mITT population, no violation of inclusion criteria, not meeting any exclusion criteria, trial treatment as randomized, time interval between Visit 2 (day 0, surgery) and Visit 7 (week 26): 22 to 30 weeks, absence of events with a strong effect on quality of life but definitely unrelated to the randomized study treatment (for example, new serious disease during post-operative follow-up, or accident).

The safety population comprises all randomized subjects who received trial treatment (autologous bone graft or Treatment with CBVF). In analyses of the safety population, subjects will be assigned to the treatment they actually received.

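### Open-label allocation precedes the reduction that creates the void, so arm-dependent decisions in theatre can remove patients from the per-protocol set that alone decides non-inferiority

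*Protocol article*

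**What the plan says.** All references are to the protocol article.

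- **Eligibility criteria:** patients with closed depression fractures (AO 41-B2 and B3) "requiring reconstruction of the subchondral bone void are enrolled into the trial".
- **Operative treatment:** "The bone defect, which is created after reduction of the depressed articular fragments, will be reconstructed either with an autologous cancellous bone graft" or with CBVF. The order of events is also stated: "After randomization, all patients will be operated as soon as possible, depending on local soft tissue conditions, hematoma, and swelling".
- **V1 - screening visit and randomization:** after radiological assessment of the fracture type comes "verification of inclusion and exclusion criteria performed", and then "The trial participant will be electronically randomized to one of the two treatment arms using a web-based tool". V1 falls within the 7 days before surgery, and Table 1 lists CT and X-ray evaluation and randomization at that visit.
- **Methods/Design:** CERTiFy "trial is a prospective, open-label, multicenter, controlled, randomized clinical trial".
- **Analysis populations:** PP requires mITT eligibility and, among other things, "no violation of inclusion criteria, not meeting any exclusion criteria, trial treatment as randomized". The mITT set requires only that PCS is available before surgery and at week 26. The ITT set keeps every randomised patient.
- **Efficacy analysis:** the PCS comparison is analysed primarily in PP. The pain test is confirmatory only if non-inferiority has been claimed there. The mITT and ITT analyses of PCS are supportive.

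**The concern.** A per-protocol comparison keeps the protection of randomisation only if the reasons for leaving the set are unrelated to the arm. Here one reason may be related to it. The surgeon knows the arm before the void exists, and filling it asks for different things in the two arms. Graft needs a second operative site at the iliac crest, with the donor-site complications listed under Background and rationale. CBVF does not. The same section says that a metaphyseal defect may accompany the depression and often, not always, requires additional reconstruction, so some variation in need is acknowledged.

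A control patient whose void is left unfilled, or filled with something other than graft, was not treated as randomised and drops out of PP. A comparable CBVF patient may well be filled as planned and stay. The ANCOVA adjusts for baseline PCS, age group and gender, none of which measures void size. The Source of bias section discusses ascertainment but not this selection. At stake are the non-inferiority claim and, through the hierarchy, the confirmatory test of pain.

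**Working it through.** **1. The plan's own figures.** Inputs from Sample size and power calculation: SD 10, margin 5, true difference 0, one-sided 2.5%, power 80%. The allocation ratio is not stated; 1:1 is assumed. The shifted t-test gives 64 per arm, 128 in total (power 80.15%; 63 per arm gives 79.5%). Then 128 / 0.95 = 134.7, so 135, or 136 as an even total. The plan's figures reproduce and there is no arithmetic error.

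**2. Sequence of events.** V1: imaging, check of criteria, randomisation. V2: reduction creates the void, and it is filled or not. Afterwards: PP membership depends on the treatment received. The arm is known throughout the last two steps.

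**3. Illustration of size.** Neither input below is in the document; both are assumptions.

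- f = share of controls who leave PP for this reason
- D = PCS gap between those who leave and those who stay
- Shift in the PP difference (CBVF minus control): s = f × D. It is positive if those who leave do better, because the PP control mean then falls, and negative if they do worse.
- SE = 10 × √(2/64) = 1.77, held fixed for simplicity
- One-sided error at a true difference of -5: 1 - Φ(1.96 - s/1.77)
- Power at a true difference of 0: Φ((5 + s)/1.77 - 1.96)

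| f | D | s | One-sided error |
|---|---|---|---|
| none | none | 0 | 2.5% |
| 10% | 3, leavers better | +0.30 | 3.7% |
| 10% | 5, leavers better | +0.50 | 4.7% |
| 15% | 5, leavers better | +0.75 | 6.2% |
| 10% | 5, leavers worse | -0.50 | 1.2% |

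For s = +0.5: 1.96 - 0.5/1.77 = 1.68, and the upper tail is 4.7%. For s = -0.5: 1.96 + 0.28 = 2.24, upper tail 1.2%; power is Φ(4.5/1.77 - 1.96) = Φ(0.59), about 72%.

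**4. With the lost patients also removed from the sample size.** Take 68 per arm, 5% lost in both arms, and a further 10% lost from one arm with a gap of 5 points. The error is 4.6% if the loss flatters CBVF, and power is 69% if it goes against CBVF. With a gap of 10 points these become 7.9% and 59%.

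**5. Room in the allowance.** The plan leaves 136 - 128 = 8 patients for every kind of PP exclusion in both arms. Ten per cent of 68 controls is about 7 patients, and 15% is about 10. The 10% case would nearly use up the allowance and the 15% case exceeds it. If total PP loss reached 10% of 136, power would be 78.3% even without selection.

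**The case against.** **No second eligibility decision.** A reader might infer that surgeons who know the arm decide in theatre who still qualifies, or who belongs to PP. The document does not say so. Criteria are verified at V1 on imaging, described before the electronic randomisation, and doubtful fracture classification is an exclusion. Nor does the document say who assigns PP membership. It also follows that an unfilled patient need not have violated the inclusion criterion, since that was judged before surgery. What is breached is treatment as randomised. This objection stands.

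**Filling is prescribed.** Operative treatment says that the defect will be reconstructed with one of the two materials, so leaving it unfilled is a deviation and not an option offered. That also stands, but deviations are exactly what the PP definition acts on. A Table 1 footnote says that no surgery is done for study purposes, which leaves some room for a surgeon to refrain from a harvest.

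**Direction.** A reader might also infer that the selection favours CBVF, because patients with small voids would do better. No passage links void size to prognosis. The Discussion reports frequent loss of reduction when these fractures are fixed without augmentation, and on that basis unfilled controls could do worse. The direction is open.

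**Supportive analyses.** The mITT set has no treatment-received condition and ITT keeps everyone, so a divergence from PP could reveal the problem. This is a real safeguard, but it does not govern the claim.

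**Conclusion.** The point holds in a limited form. Allocation is known to an unblinded surgeon before the void exists, and treatment decisions made with that knowledge feed into the only analysis set on which non-inferiority is decided. This follows from the protocol's text.

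The size does not follow from the text. With 10% of controls lost and a 5-point gap, both assumed, the one-sided error lies between about 1.2% (power about 72%) and about 4.7%, depending on whether those lost do worse or better. The frequency may be low in B2 and B3 fractures. The 7-day interval is a maximum, since surgery is to follow as soon as possible, but the sequence matters at any interval. This is a worthwhile, inexpensive improvement and not evidence that the planned result would be wrong.

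**What to change.** **Preferred, where feasible.** Keep consent and baseline assessments at V1 and release the allocation from the existing web tool at V2, once reduction is done and the surgeon has recorded that the void needs reconstruction. This takes the arm out of that judgement. It costs a protocol amendment, theatre logistics, and keeping the donor site available until allocation. As the trial is already recruiting, patients randomised under the present procedure would remain, so the second measure is needed for them in any case.

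**Otherwise.**
1. Add one eCRF item, completed before allocation from the screening imaging, recording that the void is expected to need reconstruction.
2. Do not let the claim rest on PP alone. Also require the 95% confidence interval for the PCS difference to lie above -5 in the mITT set, where patients left unfilled or filled differently stay in their randomised arm. PP is retained because treatment deviations can dilute a difference in mITT.

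The cost is the eCRF item, an amended decision rule and a slightly stricter claim. The mITT analysis itself is already planned. Both routes reduce the dependence on this selection whichever way it runs. Neither proposes a clinical rule on when a void should be filled.

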**Figure 5 F5:**
[figure not shown]
**Postoperative anteroposterior (a-p) X-ray of the knee showing the result of reconstruction.** The subchondral bone defect was filled with CBVF.

**Figure 6 F6:**
[figure not shown]
Postoperative lateral X-ray of the knee showing the reconstruction result.

### Outcome measures

#### Primary outcome

The primary endpoint in this study is the SF-12 v2 Physical Component Summary (PCS) score (4 week standard recall version) at week 26 after the intervention. The co-primary endpoint is pain VAS measurement at week 26 after the intervention. The SF-12 is a subset from items of the SF-36, which is the most widely used generic health assessment questionnaire worldwide.

#### Secondary outcomes

The SF-12v2 Mental Component Summary (MCS) at week 26 and costs of care related resources will be evaluated as key secondary endpoints.

Services relevant to cost of care will be estimated from the type of insurance (private or compulsory), days spent in the hospital as the result of the trauma, total costs of care for the hospital stay in Euro, DRG (diagnosis-related group) code and the number of lump compensations for ambulant treatment. In addition, the patient will be asked to document the costs of care for services related to trauma and applied outside the trial center (for example, physiotherapy, medical aids) beginning with the day of discharge from the trial center. The assessment of costs will be specific for local German conditions as this study will be performed in German centers only.

#### Other endpoints

SF-12v2 PCS and SF-12v2 MCS will be assessed as additional endpoints at visits 4 to 6, the pain measured by VAS (visits 3 to 6) as well as the intake of pain medication at visits 3 to 7. Fracture healing and integrity of the articular surface will be assessed using standard anteroposterior and lateral views of plain radiographs. The radiographs will be reviewed by the panel of two experienced orthopedic trauma surgeons and one consultant who will be blinded as to the kind of material used. The panel will independently review all radiographs in chronological order. The loss of reduction and subsidence of the articular surface will be recorded and analyzed using the Rasmussen score [17], in which articular subsidence, condylar widening, and varus or valgus deviation will be quantitatively assessed over a period of 26 weeks. In addition, the panel will evaluate fracture union, bone defect remodeling as well as loss or premature resorption of the graft using the following point score:

1. Osteolysis, premature resorption of the graft

2. Unchanged size of the void, no resorption of the bone graft

3. Beginning marginal bone defect remodeling

4. Bone defect remodeling with undirected formation of trabecula

5. Bone defect remodeling with directed formation of trabecula

Complications (for example, hardware failure and displacement, wound healing problems, infections, revisions, neurologic impairment, pressure ulcers and others) as well as all adverse events (AE) will be recorded and regularly evaluated throughout the study.

